# Evaluation of Various Support Intensities of Digital Mental Health Treatment for Reducing Anxiety and Depression in Adults: Protocol for a Mixed Methods, Adaptive, Randomized Clinical Trial

**DOI:** 10.2196/45040

**Published:** 2023-04-28

**Keywords:** video chat therapy, therapist assistance, self-help, transdiagnostic, digital intervention, anxiety, depression, comorbidity

## Abstract

**Background:**

Anxiety and depression are leading causes of disease worldwide, requiring timely access to evidence-based treatment. Digital mental health (dMH) interventions increase accessibility to evidence-based psychological services delivered in a variety of web-based formats (eg, self-help and therapist-assisted interventions). Robust and rigorous studies of adaptive web-based intervention designs are scarce. No identified randomized clinical trial has investigated the efficacy of a 2-stage adaptive design, whereby the program-only condition or *no support* dMH treatment program is augmented by either low or high therapist assistance, if a participant does not improve or engage in the program-only condition.

**Objective:**

The primary objective is to assess whether low or high therapist-assisted support delivered via video chat is more effective in reducing anxiety and depressive symptoms compared with a dMH program–only condition. The secondary objective is to evaluate the role of motivation; self-efficacy; and preferences in participant engagement, adherence, and clinical outcomes (anxiety and depression symptoms) among the 3 treatment conditions (program only, low-intensity therapist assistance, and high-intensity therapist assistance). A mixed methods analysis of factors affecting participant attrition, participant reasons for nonengagement and withdrawal, and therapist training and implementation of dMH interventions will be completed. Qualitative data regarding participant and therapist experiences and satisfaction with video chat assessment and treatment will also be analyzed.

**Methods:**

Australian adults (N=137) with symptoms or a diagnosis of anxiety or depression will be screened for eligibility and given access to the 8-module Life Flex dMH treatment program. On day 15, participants who meet the augmentation criteria will be *stepped up* via block randomization to receive therapist assistance delivered via video chat for either 10 minutes (low intensity) or 50 minutes (high intensity) per week. This adaptive trial will implement a mixed methods design, with outcomes assessed before the intervention (week 0), during the intervention (weeks 3 and 6), after the intervention (week 9), and at the 3-month follow-up (week 21).

**Results:**

The primary outcome measures are for anxiety (Generalized Anxiety Disorder–7) and depression severity (Patient Health Questionnaire–9). Measures of working alliance, health status, health resources, preferences, self-efficacy, and motivation will be used for secondary outcomes. Qualitative methods will be used to explore participant and therapist experiences of video chat assessment and treatment, participant reasons for withdrawal and nonengagement, and therapist training and implementation experiences. Data collection commenced in November 2020 and was completed at the end of March 2022.

**Conclusions:**

This is the first mixed methods adaptive trial to explore the comparative efficacy of different intensity levels of self-help and a therapist-assisted dMH intervention program delivered via video chat for adults with anxiety or depression. Anticipated results may have implications for the implementation of dMH interventions.

**Trial Registration:**

Australian and New Zealand Clinical Trials Registry 12620000422921; https://tinyurl.com/t9cyu372

**International Registered Report Identifier (IRRID):**

RR1-10.2196/45040

## Introduction

### Background

The Global Burden of Diseases, Injuries, and Risk Factors Study 2019 identified depression and anxiety disorders as the 2 most debilitating mental disorders worldwide [1]. A recent study by Collaborators Cochrane Mental Disorders [2] quantified the global impact of COVID-19 on the prevalence of depression and anxiety disorders. That study estimated, for depression, an international prevalence of 246 million people (increase from 193 million people before the pandemic) and, for anxiety disorders, a prevalence of 374 million people internationally (increase from 298 million people before the pandemic). Such statistics demonstrate that anxiety and depressive disorders are leading diseases on a global scale that become more prevalent during global events such as the COVID-19 pandemic.

Rates of help seeking for a mental health–related service have also increased in light of the COVID-19 pandemic [3]. There has been increased use of digital mental health (dMH) interventions and telehealth services, attributable first to their ability to disseminate and scale quickly and, second, to their utility as an adjunct to existing face-to-face mental health services [4]. However, long wait lists to access psychological treatment via telehealth are reported [5,6], as are substantial costs associated with the delivery of psychological services via telehealth [3].

To ensure access to evidence-based treatment for the wider community, empirical research conducted over the past 20 years has investigated different methods of delivering psychological treatment. As an alternative to the standard in-person, face-to-face model, dMH interventions now have a well-established evidence base for the provision of psychological treatment for anxiety and depression delivered via the internet, in a variety of formats (eg, self-help and therapist-assisted interventions), mitigating the increasing demands for mental health services.

The dMH interventions serve to increase accessibility to evidence-based services within a high-volume, low-intensity treatment model [7]. Low-intensity treatment models have been developed to assist individuals experiencing mild to moderate psychological difficulties and propose that more intensive treatment regimens could then be provided to individuals who do not benefit from less intensive forms of psychological treatment [8]. The dMH interventions can address the evolving needs of consumers by adapting the implementation of treatment such that individuals can be *stepped up* to receive high-intensity treatment if required.

Adaptive intervention treatment designs use decision rules to determine whether and how the delivery of a course of treatment is altered [9]. Stepped care models are identified as a type of adaptive intervention design. Stepped care models incorporate a low-intensity intervention that is increased if certain criteria are fulfilled and can often include augmenting, switching, or maintaining a course of treatment based on some type of consumer characteristic (ie, low engagement levels) or response (ie, symptom severity) [9]. Within a stepped care model, dMH interventions are offered as part of the first step of self-management (eg, self-help web-based program), and if required, an individual’s treatment can be increased, whereby a therapist is added to support the dMH intervention.

Previous empirical studies investigating the effectiveness of therapist-assisted dMH interventions for anxiety and depression have largely used telephone, instant messaging, and email assistance. Recent advances in dMH include the use of video chat technology, in which face-to-face synchronous digital communication most closely aligns with the traditional in-person, gold-standard service delivery model in psychology. Empirical investigation into the efficacy of video chat, compared with that of other dMH care models for treating anxiety and depression, is lacking. Most of the research studies completed so far have investigated posttraumatic stress disorder and have compared psychiatric treatment delivered via video chat with that delivered in-person, with comparable outcomes reported [10,11].

Currently, there is a paucity of robust and rigorous studies on the use of video chat methods in dMH interventions. No identified clinical trial has investigated the efficacy of a 2-stage adaptive design offering the *no therapist support* dMH program and augmenting a participant’s program with either low or high therapist assistance if they do not improve or engage in the *no therapist support* program-only condition. Within the field of psychology, the literature about dMH is also largely biased toward quantitative research methodology that minimizes the opportunity to more closely investigate factors contributing to the efficacy of various intensities of a dMH treatment program (eg, participant attrition and engagement factors). Therefore, the testing of an adaptive, mixed methods randomized clinical trial design will provide great insight into participant characteristics of engagement; efficacy of video chat as a mode of therapist assistance in dMH interventions; and, overall, improvement of future services delivered via dMH.

### Objectives

The purpose of this study is to present a protocol designed to evaluate various support intensities of a dMH treatment program for anxiety and depression within a mixed methods design. Therefore, the study has the following primary objectives:

To compare the efficacy of clinical outcomes (anxiety [Generalized Anxiety Disorder–7; GAD-7] and depression [Patient Health Questionnaire–9; PHQ-9] symptoms) among the 3 treatment conditions (dMH program only, low-intensity therapist assistance, and high-intensity therapist assistance), with particular focus on whether therapist-assisted support produces greater reductions in anxiety and depression severity compared with those produced by dMH program–only support.To examine the role of motivation and self-efficacy on engagement, adherence, and clinical outcomes (anxiety [GAD-7] and depression [PHQ-9] symptoms) among the 3 treatment conditions (dMH program only, low-intensity therapist assistance, and high-intensity therapist assistance) at postintervention (week 9) and follow-up (week 21) assessments, compared with those at preintervention (week 0) assessment.To explore participant and therapist experiences and satisfaction with assessment and therapist assistance delivered via video chat technology, using semistructured interviews; specific areas of focus will include the ability to develop and maintain therapeutic relationships, implementation barriers and facilitators, and identified strengths and limitations of video chat technology for conducting assessments and delivering dMH treatment.To explore therapist training and implementation experiences in the delivery of dMH interventions.To use a mixed methods analysis to examine factors affecting participant attrition in each of the treatment intensities; quantitative examination of preferences, treatment condition allocation (dMH program only, low-intensity therapist assistance, and high-intensity therapist assistance), and attrition rates will be explored; qualitative exploration of participant reasons for withdrawal and nonengagement with therapist support will also be conducted using semistructured interviews.To explore the outcomes of working alliance, health resources, and health status among the 3 treatment conditions (dMH program only, low-intensity therapist assistance, and high-intensity therapist assistance).

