### Randomization

The process of randomly allocating participants to either the low-intensity or high-intensity treatment groups will comply with CONSORT guidelines. A block randomization design will be used to randomly allocate each participant to either the low-intensity or high-intensity therapist assistance condition throughout the trial. Random allocation will occur when a participant has met the criteria to be *stepped up* to have their Life Flex program augmented with therapist assistance. Participants will be aware of the group they have been randomly allocated to but will remain unaware of the study’s objectives. The provisional or general psychologists will not be blinded to the treatment conditions, as they will need to adhere to either the support or the therapist role.

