### Sample Size Calculation

Only aggregate data will be used for the main analysis. Assuming a conservative medium effect (ie, GPower f[v] test=0.25), significance set at 5% (*P*=.05), and power at 80%, 98 cases are required to demonstrate statistical significance in the primary outcome measures. However, allowing for a 30% attrition rate [26], a total target sample size of 137 participants will be required.

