The findings of the trial have the potential to contribute toward the evidence base of adaptive treatment designs for anxiety and depression, with considerable implications for the implementation of stepped care models in dMH. As the study will evaluate outcomes of health resources and health status among the 3 treatment conditions, it is anticipated that the study results will enhance our understanding of participant needs and resources required at the self-help (dMH program only; step 1) and therapist-assisted (low and high therapist assistance; step 2) levels in the context of an adaptive intervention design.

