### Conclusions

This protocol outlines the first adaptive mixed methods clinical trial design investigating the efficacy of a 2-stage adaptive dMH intervention program incorporating both low-intensity and high-intensity therapist assistance delivered via video chat technology, compared with program-only support. This trial adds to the existing studies on dMH interventions and provides further understanding of participant and therapist experiences and satisfaction with video chat assessment and therapist assistance, along with therapist training and implementation experiences. Outcomes are expected to have implications for stepped care models and wide dissemination of dMH interventions for anxiety and depression.

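### No stated analysis estimates the outcome under either stepped-care strategy that the randomisation creates, and the claimed effect of the adaptive program against program only cannot be identified

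*Protocol article*

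**What the plan says.** The Conclusions section describes the trial as "investigating the efficacy of a 2-stage adaptive dMH intervention program" and gives program-only support as the comparator. Principal Findings expects "considerable implications for the implementation of stepped care models in dMH".

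The Objectives section frames the primary comparison differently, as one "among the 3 treatment conditions (dMH program only, low-intensity therapist assistance, and high-intensity therapist assistance), with particular focus" on therapist-assisted against program-only support. The hypothesis in Principal Findings is the same contrast. That section adds that low and high assistance will also be compared, and it makes the case for low-intensity support depend on that comparison. The Results section plans two contrasts of change from baseline to weeks 9 and 21 in a mixed model, without naming the groups contrasted.

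On allocation, the Randomization section says: "A block randomization design will be used to randomly allocate each participant to either the low-intensity or high-intensity therapist assistance condition". It fixes the moment: "Random allocation will occur when a participant has met the criteria to be *stepped up". No allocation ratio is given. The Life Flex Program–Only Condition section keeps people who improve or engage on the program alone. Results reports that 73 of 113 met the step-up criteria and 40 did not.

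**The concern.** Stepped care is a rule applied from the first day: everyone starts on the program, and support is added if a trigger is met. Its effect is the average outcome over everyone who starts, including those who never need support. With one randomisation after the trigger, the design contains exactly two such rules, and participants who stay on program only follow both.

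The stated objective treats the three end states as parallel groups instead. The therapist versus program-only contrast sets people who triggered step-up against people who improved or engaged, so it describes neither strategy. Dropping that contrast would not solve the problem, because there would still be no expected week-9 or week-21 score for a person starting either strategy. A service deciding whether and how to run stepped care needs that score.

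**Working it through.** **Inputs.** From Results: 113 starters, 73 stepped up, 40 not. From Sample Size Calculation: f(V) = 0.25, 5% significance, 80% power, 98 cases, 30% attrition, 137 in total. Assumed: 1:1 allocation (37/36), since no ratio is stated, and outcome SDs as given below.

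**1. The plan's own figure.** The text has "Assuming a conservative medium effect (ie, GPower f[v] test=0.25" and "significance set at 5% (*P*=.05), and power at 80%, 98 cases are required". The numbers of groups and occasions are not stated. A repeated-measures MANOVA interaction with k = 3 conditions and m = 3 occasions (weeks 0, 9, 21) gives:
- s = min(k−1, m−1) = 2 and df1 = 2 × 2 = 4
- df2 = 2 × (98 − 3 − 2 + 2) = 190
- λ = 2 × 98 × 0.25² = 12.25
- power 0.800, with N = 98 the smallest N that reaches 80%

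This fits sizing on the three end states but does not prove it, since other layouts come close (96, 97, 100, 101). The 137 matches 98 × 1.4 = 137.2; dividing by 0.7 would give 140.

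**2. The two strategies.** Let p = 73/113 = 0.646 and 1 − p = 40/113 = 0.354.
- Mean under program-then-low = 0.354 × (stayers) + 0.646 × (low)
- Mean under program-then-high = 0.354 × (stayers) + 0.646 × (high)
- Difference = 0.646 × (low − high)

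The stayers cancel in the difference. A 2-point low-high difference becomes 0.646 × 2 = 1.29 points per starter. About 77 (40 + 37) and 76 (40 + 36) of the 113 are consistent with each strategy.

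**3. What the objective's contrast gives instead.** Take assumed changes of −6 (stayers), −3 (low) and −4 (high). The strategy means are −4.06 and −4.71, differing by 0.65. Pooled therapist minus program only is −3.5 − (−6) = +2.5, which appears to count against support and matches neither strategy.

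**4. Precision, full data.**
- SE of low − high = √(1/37 + 1/36) = 0.234 SD
- SE of the strategy difference, share taken as fixed = 0.646 × 0.234 = 0.151 SD
- Allowing for the estimated share adds (low − high)² × 0.646 × 0.354/113 to the variance. At a difference of 0.5 SD this is 0.0005 on top of 0.0229, so the SE is 0.153 SD
- SE of one strategy mean is about 0.12 to 0.13 SD

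The 95% half-width of the strategy difference is 1.96 × 0.151 = 0.30 SD. With 26/25 analysed (30% attrition) it is 1.96 × 0.646 × √(1/26 + 1/25) = 0.35 SD. At an assumed SD of 5 points these are 1.5 and 1.8 points. For SDs of 4 to 6 they run from 1.2 to 1.8 and from 1.4 to 2.1.

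Power for low versus high at 0.5 SD is 56% with 73 participants and 42% with 51.

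**5. Adaptive program against program only.** This needs the outcome of triggered participants left without support. By design there are none.

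**The case against.** The strongest reply is that the choice between the strategies already has an estimate. Principal Findings plans low versus high, which is randomised. Multiplying it by 0.646 changes neither the sign nor, in essence, the test. This stands. A reader might infer that the stepped-care conclusions have no estimate behind them, or that the trial cannot report the strategy outcomes; the documents do not support either. The shares are published, and the strategy means follow from the three condition means.

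A reader might also infer that every planned analysis compares end states. That over-reads Results: the two contrasts do not name their groups, and reliable change is planned for participants without a stated comparison. Nor is low versus high among the stepped-up an overstatement. It is the effect in those for whom the choice arises, which is a different average from the effect per starter.

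Two further points carry some weight. The stepped-care implications in Principal Findings are worded as potential, and the aim given in Objectives is to evaluate support intensities. Also, a supplementary estimand could sit in an analysis plan that is not shown. That plan cannot, however, repair a stated objective and hypothesis that target neither strategy, or a Conclusions section that claims efficacy of the adaptive program against program-only support.

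**Conclusion.** The concern holds in a limited form. The difference between the two strategies has an estimate, though an imprecise one: 0.646 times a randomised low-high difference with 42% to 56% power at 0.5 SD. Two things lack a stated estimate. The first is the mean outcome under each strategy, which the data identify. The second is the effect of the adaptive program against program only, which this design cannot identify.

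The step-up share rests on the reported counts. The precision figures rest on assumed 1:1 allocation and an assumed SD. Each strategy is also not uniquely defined at present, because Trial Design and the Life Flex Program–Only Condition section describe the symptom triggers differently: deterioration of more than 5 points in the first, no change in symptoms in the second.

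**What to change.** - In Results, name low versus high among the stepped-up as an explicit randomised contrast.
- Add mean GAD-7 and PHQ-9 change at weeks 9 and 21 for each strategy in all 113 starters. One route is the average of the mixed-model condition means weighted by enrolment shares (40/113 stayers, 73/113 low or high). The other is weighting by the inverse of the actual allocation probability, which gives a weight of 2 only if allocation was 1:1.
- If weighting is used, handle dropout as well. With an assumed 40% loss among the stepped-up and 10% among stayers, 43.8 and 36.0 remain, and the step-up share falls from 0.646 to 43.8/79.8 = 0.55.
- Report the strategy difference with a standard error that allows for the estimated share.
- Reconcile the two descriptions of the step-up criteria, so that each strategy has one definition.
- Label the analysis post hoc if it is added now, since data collection has ended and results have been accepted for publication.
- Limit the stepped-care statements in Principal Findings and Conclusions to the comparison of the two strategies, and withdraw the claim of efficacy against program only.

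The cost is a little more analysis on data already collected. The strategy difference will be smaller than the low-high difference and carries no more power.

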## Methods

### Trial Design

This trial will follow the International CONSORT (Consolidated Standards of Reporting Trials) guidelines and evaluate the conditions using an adaptive randomized clinical trial design [12]. The clinical trial also adheres to SPIRIT (Standard Protocol Items: Recommendations for Interventional Trials; Multimedia Appendix 1). All information will be strictly confidential, yet subject to legal limitations (eg, legal subpoena), and only accessed by the investigators. Data are stored securely using 256-bit encryption Secure Sockets Layer and Transport Layer Security software when information is transmitted. Any hard copy data will be stored securely in lockable filing cabinets at the Federation Community Psychology Services at Federation University.

Eligible participants will be given access to a self-help dMH treatment program (Life Flex) and have their symptoms of anxiety or depression evaluated at day 15 to assess whether they meet the criteria to have their treatment program augmented with therapist assistance. Participants will be considered as eligible to be *stepped up* to a therapist-assisted condition if they meet any of the following criteria: they have not read the introduction module or module 1 of the Life Flex program; have symptoms of anxiety or depression that have deteriorated by >5 points (as assessed by comparison of their baseline depression [PHQ-9] and anxiety [GAD-7] scores against their week-3 scores); show symptom improvement, but their scores remain in a severe range; and are yet to complete the week-3 questionnaire assessment.

Outcomes will be assessed before the intervention (week 0), during the intervention (weeks 3 and 6), after the intervention (week 9), and at the 3-month follow-up (week 21). Results will be disseminated via publication. Figure 1 illustrates the study’s design and expected participant flowchart.

